**Methods and analysis:**

A randomised, two-arm feasibility trial involving allocation of patients to either a treatment group (positive psychotherapy) or control group (treatment as usual) group, according to a 1:1 ratio. A total of 60 participants at three sites will be recruited including 20 participants at each site. Assessments will be conducted at baseline, on completion of the 8-week intervention and 3 months following completion. These will include a range of questionnaire-based measures, psychophysiology and qualitative outcomes focusing on feasibility outcomes and participant experience. This study has been approved by the Wales Research Ethics Committee (IRAS project ID: 271,251, REC reference: 19/WA/0336).

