#### Additional inclusion criteria for mentors

Mentors will be subject to the same inclusion criteria as participants. They will also be subject to the following additional inclusion criteria:Known to and recommended by their referring clinical teamDemonstrated ability to be responsive and sensitive to the needs of othersGood interpersonal skillsWilling and able to commit to training as well as attending all eight treatment sessions

A total of six mentors will be recruited including two mentors per health board.

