### Design

The study will randomly allocate eligible patients to either the treatment (positive psychotherapy [PP] intervention) or control (TAU) at a 1:1 ratio with stratification by site and antidepressant use (yes/no) (see further details below under ‘Randomisation’). The choice of a TAU control condition was based on ethical considerations and also enabled comparisons with past research [10, 11, 13]. Data collection will take place at each of the three healthcare sites, capturing a diverse representation of patients and enhancing the generalizability of the findings beyond a single site.

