### Randomisation

Participants will be randomly allocated to the intervention or TAU using REDCap [22, 23]. An authorised person will access REDCap to determine allocated treatment once eligibility has been confirmed. The participant will be notified of the allocation and the days on which the intervention will be delivered (if randomised to the intervention arm). The randomisation algorithm will be designed to promote balance in the sample sizes of the intervention and control groups, although exact numbers may vary slightly due to stratification for site (i.e. 3 sites; aiming for 10 participants per site, per arm) and antidepressant use (i.e. yes/no; aiming for an equivalent number of participants prescribed antidepressants per site, per arm).

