### Procedure

The study will involve the following key stages (see also Fig. 1, Table 2):*Referral*: Potential participants and mentors will be asked whether they would like to participate in the study and will be given the participant or mentor information sheet as appropriate.*Consent*: Potential participants and mentors meet a member of the research team to discuss the study and provide consent.*Eligibility*: Potential participants and mentors meet with the research assistant (under the supervision of a clinical psychologist) to determine eligibility for the study. If participants are deemed ineligible, they will be followed up by the PI and an explanation given.*Baseline measures*: Eligible participants and mentors meet with the research assistant to complete baseline measures. A detailed description of the measures are provided below.*Randomisation*: Participants will be randomly assigned to the TAU control group or the PP intervention group. Two mentors will be assigned to each of the three intervention groups based on availability and proximity.*Treatment*: Participants and mentors attend the 8-week PP group or TAU control.*Immediate follow-up*: All participants meet the research assistant to repeat quantitative measures over a 2-week period following the final session of the 8-week-positive psychotherapy intervention. Group attendees and mentors will also be invited to take part in participant and mentor focus groups, respectively, to gather data for qualitative analysis.*Three-month follow-up*: All participants meet the research assistant to repeat quantitative measures a final time, 3 months following the final session for the intervention.

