### Quantitative data

This feasibility trial will explore the most appropriate primary outcome for a fully powered RCT. Data analysis, following intention-to-treat principles, will focus on descriptive statistics and feasibility outcomes, consistent with the primary aims and objectives of the trial. Summaries, including completeness, for outcome measures and important demographic covariates will be reported by group. No missing data will be imputed. While clinical effectiveness will not be definitively assessed at this stage, we will explore hypotheses that measures of depression, anxiety and stress (as operationalised by the DASS) will diminish, and measures of PERMA and HRV will improve, using a split-plot ANOVA with group (intervention vs control) as a between-subjects factor across time (pre vs two follow-up assessments), a within-subject factor. All assessments will be summarised using two-sided tests and 95% confidence intervals where appropriate. Estimates of treatment effect size and intraclass correlations will be used to inform sample size considerations for a full-scale RCT.

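### The plan does not say which intraclass correlation will inform the RCT sample size, and a therapy-group or site ICC from three groups, one per site, is too imprecise for that use

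*Protocol article*

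**What the plan says.** The Quantitative data section commits to a use: "intraclass correlations will be used to inform sample size considerations for a full-scale RCT". It does not define the ICC. The only model named is a split-plot ANOVA of arm by time, and no site or therapy-group term is mentioned.

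Three places fix the number of therapy groups:
- Procedure: "Two mentors will be assigned to each of the three intervention groups based on availability and proximity".
- Randomisation: "3 sites; aiming for 10 participants per site, per arm".
- Additional inclusion criteria for mentors: "A total of six mentors will be recruited including two mentors per health board".

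The article does not state outright that each site runs one group, but these statements together leave no other natural reading. The Participants section mentions two courses per year as past clinical practice, which adds no groups to this trial. Allocation is 1:1 within site (Design), so each site also has about 10 TAU participants. The footnote to Table 2 says that they do not attend the study meetings. The Treatment as usual section allows some usual-care treatments to be given in groups.

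**The concern.** Participants treated together in a group tend to have correlated outcomes, and a full RCT of group therapy needs an allowance for this. The allowance is the design effect, which depends directly on the ICC. An ICC taken from three groups says almost nothing about its true size. About half the time it would come out at or below zero, which could be read as permission to plan the RCT with no allowance. In other trials it would come out so large that the RCT looked unaffordable. Because the plan does not say which ICC it means, a reader cannot tell whether the stated use is sound (within participant) or unsupported (therapy group or site).

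**Working it through.** **Inputs from the protocol.** 3 sites × 2 arms × 10 = 60, which matches the stated total: "A total of 60 participants at three sites will be recruited including 20 participants at each site". Therapy groups k = 3, group size m = 10. Table 3 passes attrition below 40%, so groups could shrink to about m = 6.

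**Assumptions.** The protocol gives no ICC, design effect or RCT effect size. ICC values of 0.05 and 0.10, and a standardised effect of 0.4, are used for illustration only.

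**1. Precision of a therapy-group ICC** (one-way ANOVA estimator, exact F-based interval, 2 and 27 df)
- F = 1 + m × ICC/(1 - ICC) = 1 + 10 × 0.05/0.95 = 1.526.
- Each limit is (F/q - 1)/(F/q + 9), where q is the 97.5% or 2.5% point of F on 2 and 27 df (4.242 and 0.02534).
- Lower limit: 1.526/4.242 = 0.360, giving (0.360 - 1)/(0.360 + 9) = -0.07.
- Upper limit: 1.526/0.02534 = 60.2, giving (60.2 - 1)/(60.2 + 9) = 0.86.
- An observed ICC of 0.10 gives -0.05 to 0.89.

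**2. Chance of an estimate at or below zero when the true ICC is 0.05**
- The mean-square ratio is 1.526 times an F variable on 2 and 27 df. The estimate is zero or negative when that variable is at most 1/1.526 = 0.655.
- With 2 numerator df the probability is 1 - (1 + 2 × 0.655/27)^(-13.5) = 0.47.
- Simulation (100,000 runs) agrees: 47%, with a central 95% range of the estimate of -0.11 to 0.35. At m = 6 these become 52% and -0.19 to 0.47.

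**3. What this means for sizing an RCT**
- Design effect at m = 10: 1 + 9 × 0.05 = 1.45 at the point estimate, 1 + 9 × 0.856 = 8.70 at the upper limit, and 1.0 if the estimate is taken as zero.
- At an assumed effect of 0.4 with 80% power, 99 per arm are needed without clustering. With clustering in one arm and equal arms, the multiplier is (1 + design effect)/2. That gives 99 × 1.225 = 122 per arm at the point estimate and 99 × 4.85 = 481 per arm at the upper limit.
- About 40 groups of 10 would be needed to narrow the CI to roughly 0.00 to 0.14 at an observed 0.05.

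**4. Can site be separated from group?**
- Within the intervention arm, no: each site has one group.
- With the TAU arm, an additive site effect cancels in the within-site arm difference. Simulation with site variance 0.05, group variance 0.05 and total variance 1 recovers the group component without bias (mean about 0.05). It is negative in 54% of trials, with a central 95% range of about -0.20 to 0.67.
- What remains mixed with the group effect is any site-by-treatment interaction, including facilitator and mentor effects.

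**5. Within-participant ICC for contrast** (three visits, two arms)
- An observed 0.50 gives F = 1 + 3 × 0.5/0.5 = 4 on 58 and 116 df, with a 95% CI of 0.35 to 0.64. With 36 participants (60 × 0.6) it is 0.30 to 0.68. Either is usable.

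**6. Effect on a simple arm difference in this trial**
- With an ICC of 0.05 in one arm only, the true variance is (1 + 1.45)/2 = 1.225 times the naive value. The naive variance is therefore 1 - 1/1.225 = 18% too low.

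**The case against.** The strongest reply is that the sentence may mean something else. It follows closely on the description of a repeated-measures analysis, and a within-participant ICC is an ordinary planning input that this trial can estimate. That stands, and it is why the point is conditional and why the first remedy is to name the ICC.

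The protocol also says only that the estimates will inform sample size considerations. It does not commit to using a point estimate alone, or to dropping the clustering allowance if the estimate is negative. That stands too: the harm is a risk that the wording leaves open, not a stated plan.

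A reader might infer three stronger things that the document does not support.
- *That the ICC cannot be estimated at all.* A number and an exact interval can be computed. The fault is precision.
- *That group and site are inseparable.* This is true only within the intervention arm. Randomisation within site provides a TAU comparison that removes an additive site effect.
- *That the trial's own tests are invalid.* The ANOVA is expressly exploratory, and no progression criterion in Table 3 uses it. The 18% figure applies to a simple difference of means, not to the arm-by-time test. Omitting site can also widen intervals, which works in the other direction. Model covariates are commonly left to an analysis plan, so including site is offered as an easy improvement, not charged as an omission.

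Nor can it be assumed that clustering arises only in the intervention arm, because usual care may include group treatments.

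**Conclusion.** The point holds in a limited form. The ICC is undefined. If it is a therapy-group or site ICC, three groups cannot give a value fit to set the RCT's design effect: the 95% CI at an observed 0.05 spans about -0.07 to 0.86, and an estimate at or below zero is nearly as likely as not when the truth is 0.05. These figures rest on full groups of 10 and an assumed ICC of 0.05, and attrition makes them worse. If a within-participant ICC is meant, the precision objection falls away, although an RCT of group therapy would still need a clustering allowance from another source. The primary feasibility conclusions do not depend on any of this.

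**What to change.** In the Quantitative data section:
1. State which ICC is meant: within participant, therapy group or site.
2. Report any therapy-group ICC only with its CI, and say that its point estimate will not set the RCT design effect.
3. Say that the RCT will be planned over a range of ICC values justified from outside this trial, with the allowance applied to the group-therapy arm, and to TAU only if TAU is also delivered in groups.
4. Add site, already a stratification factor, to the exploratory arm-by-time model, and state that CIs for arm differences do not allow for therapy-group clustering.

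The cost is a few sentences, with no change to recruitment, data collection or Table 3. The later RCT may be planned somewhat larger.

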### Qualitative data

The embedded qualitative aspect of the study will be based on a critical realist perspective, in which the acceptability and experience of the trial and intervention are embedded in the social contexts of participants. This means data analysis will attend to both the manifest content of interviews to ascertain concrete feedback regarding procedures, as well as being sensitive to the contextual features that shape people’s experiences and views.

We will adopt a pragmatic, reflexive and critical realist stance, analysing the qualitative data using reflexive thematic analysis (RTA) [34, 35]. Data analysis will explore key themes/codes using organic and open-ended coding, theme refinement and recursivity of analytic phases, facilitating prolonged and deep engagement to produce a meaningful and useful analysis. Coding will proceed according to the steps of RTA. We will seek sufficient coherence across codes to address the study aims regarding acceptability and experience of trial procedures and the intervention within the sample. However, we will not set a cut point for sampling or analysis based on the concept of data saturation, consistent with RTA guidelines [36]. Coding will be conducted by one researcher after which codes will be reviewed and discussed with other members of the team who will sense-check themes and offer alternative interpretations of the data with the aim of developing richer meanings.

In line with a critical realist approach, attention will be paid to how perspectives might be shaped by social context — for example whether differences emerge across study sites or social demographics. This approach will help to understand the different ways in which social factors might impact on procedures for the conduct of a future full trial. Prolonged and deep engagement with the data, transparency of the analytic process, support for reflexive practice through use of a journal and reflexive supervision, charting of the coding process and clear characterisation of participants and data collection contexts will contribute to achieving credibility, transferability, dependability and confirmability of data and methods, consistent with Lincoln and Guba’s evaluative criteria [37].

### Health economic evaluation

We will examine the feasibility of collecting the data required for a full economic evaluation to determine the cost-effectiveness of PP compared to TAU in a future RCT. We will provide a provisional description of the resource use and costs of the PP intervention compared to TAU from an NHS and personal social services (PSS) perspective. A cost consequence analysis will be undertaken, and the costs of PP will be tabulated and described against TAU, to inform the costs and outcomes that will be the most relevant in a future definitive trial.

### Analysis of mentor data

The primary aim of this study is to explore the feasibility aspects of the study, including the recruitment and acceptability of recruiting two mentors per site. We will also calculate effect sizes from the data obtained from the six mentors, and these calculations will be exploratory in nature, given the context of a feasibility study. The primary purpose here is to gather preliminary data that will inform the design of a full-scale randomized controlled trial. We will also conduct qualitative evaluations to delve into themes that emerge from focus groups conducted with the mentors. This qualitative aspect will provide deeper insights into the mentors’ experiences and perspectives, which quantitative data alone might not fully capture. The feasibility of recruiting and engaging two mentors per study is a key aspect we aim to assess. Understanding whether this approach is practical and acceptable to the mentors themselves is vital for the successful implementation of the full-scale trial.

### Data preservation and accessibility

All patient-identifiable information stored in the NHS (with the exception of entries in clinical notes) will be destroyed within 5 years of the start of the study. Fully anonymised data will be made open access once the trial ends, consistent with developments in the open science movement.

## Discussion

This feasibility study will provide a comprehensive evaluation of the essential components necessary for the successful execution of a future trial. These components include recruitment, compliance, randomization, data collection and analysis procedures, research governance and trial management. By conducting this study, valuable insights and knowledge will be generated, serving as the foundation for determining the feasibility of conducting a future definitive randomized controlled trial.

## Data Availability

Not applicable.
